## Abstract

**Background::**

Recent novel surgical techniques for resection of low rectal cancer have been introduced and these approaches have the potential to overcome anatomical limitations like obesity, narrow male pelvis and bulky and low tumours. Two of these procedures are robotic low anterior resection (RLAR) and transanal total mesorectal excision (TaTME).

Both approaches have distinct advantages and limitations. There has been no head to head trial comparing RLAR and TaTME for patients with mid to low rectal cancer undergoing surgery by experienced surgeons. Previous studies looking at the oncological outcomes of either TaTME or robotic TME included many centres where the surgeons were on a learning curve and hence the true oncological outcomes and clinical benefits can not be measured accurately.

**Method::**

The inclusion criteria include experienced surgeons defined as minimum of 60 prior procedures with RLAR or TaTME. Successful oncological and clinical outcomes are defined as circumferential resection margin (CRM) ≥1 mm with limited postoperative morbidity (absence of Clavien-Dindo grade III–IV complications within 30 days after surgery). Local and distal recurrence rates with DFS over 3 years will be measured as primary outcome.

Data will be collected prospectively and entered in a dedicated database.

**Discussion::**

The primary objective of this study is to conduct a multicentre prospective trial to investigate clinical outcomes, in particular disease free survival (DFS) in patients undergoing RLAR and TaTME. The additional goal is to investigate other efficacy measures, complications rates, health economic aspects and patient reported health related quality of life.

This paper describes an important trial conducted in expert centres to establish the needed knowledge for a detailed comparison of outcomes for TaTME versus RLAR.

This trial is the first comparative study, comparing TaTME and RLAR, seeking to establish foothold for tailor-made surgical treatment of low rectal cancer patients.

**Trial registration::**

The trial is registered in *clinicaltrials.gov* September 2019. *Clinicaltrials.gov* id: NCT04200027.

## Background

The outcome of surgery for rectal cancer has improved substantially during the past two decades due to the introduction of the TME technique, which involves complete removal of the mesorectum with preservation of the pelvic autonomic nerves. Local recurrence rate of rectal cancer has been reduced [1] because discontinuous cancer cells in the mesorectum are removed by complete resection of this tissue [1,2,3].

Minimally invasive surgery is taking over as the preferred approach for colorectal diseases. Recently published randomized clinical trials (RCTs), such as COLOR II, COREAN and CLASICC, have shown better results for laparoscopic total mesorectal excision in terms of short-term and long-term outcomes, when compared with open TME [4,5,6].

Sphincter saving TME surgery of ultra low rectal cancer is technically demanding and hold a higher risk of incomplete resection. It is offered to a small fraction of patients in few dedicated centres. TME is limited in patients with low rectal cancer, who require surgeons with experience in ultra-low sphincter-saving laparoscopic surgery, which has a high risk of leaving a positive circumferential resection margin (CRM). In addition, narrow pelvic anatomy; male sex and high body mass index (BMI) are also unfavourable patient characteristics for a laparoscopic approach.

The wish to overcome these challenges has motivated surgeons to explore alternative techniques. The two more recent procedures that have been introduced are robotic low anterior resection (RLAR) and Transanal Total Mesorectal Excision (TaTME). These two new procedures have the potential to overcome anatomical limitations like obesity, narrow male pelvis and bulky and low tumours.

Transanal assissted TME (TaTME) combines the TAMIS (transanal minimally invasive surgery) and trans-abdominal approaches to successfully perform the TME. TaTME typically starts low in the pelvis and progresses to the mobilization of the splenic flexure/sigmoid colon in a “bottom-up” manner [7]. A single-incision laparoscopic surgery port is introduced into the anal canal to gain endoscopic access to the rectum, pneumorectum is established, A purse-string suture is applied below the tumor to ensure an adequate distal margin [8]. Transanal excision is subsequently performed with laparoscopic instruments.

Rectal distension with CO_2_ combined with magnifying optics permits excellent visualization of tissue planes. Easier access to the low rectum and precise selection of the distal resection margin under direct visualization helps ensure an adequate margin. It has been argued that TaTME may lead to a safer anastomosis by avoiding the multiple stapler firings often required in the laparoscopic approach and may result in higher rates of sphincter preserving surgery.

The robotic approach has been subject to much interest in recent years because of its potential learning benefits and clinical benefits to the patients. Some of the clinical benefits include shorter hospital stay and improved functional outcomes compared to laparoscopic surgery [9].

These advantages provided by the robotic platform hold the potential to provide improved clinical outcomes [10,11,12].

Both of the mentioned procedures have been compared retrospectively to open and conventional laparoscopic surgery in more trials showing that these methods are safe and feasible [8,13]. However direct comparison of these two techniques are still lacking.

### Potential benefits of robotic rectal resections

#### Technical Benefits

The potential benefits of robotic systems over laparoscopic TME include superior three-dimensional vision, seven degrees of freedom of movement replicating the surgeon’s hand movements made outside the field of the operation, elimination of tremor and superior ergonomics, suggesting possible application in both routine and more difficult cases.

#### Operator Learning Benefits

The main criticisms of robotic TME are the longer operating times and higher costs, compared to laparoscopic TME [13]. More widespread use of and familiarity with the robotic system has led to significant improvements in operation time, rates of conversion to open surgery and the number of harvested lymph nodes.

Bokhari et al. [14] suggested that the learning curve of robotic colorectal surgery was passed at 15 to 25. Kim et al. showed that the learning curve plateaued after 65 cases for Laparoscopic TME as opposed to 32 cases for Robotic TME [15].

Most studies to date about RLAR were done using the da Vinci Si system or older models. With the newer systems X or Xi, and once the surgeons have achieved at least 60 procedures we believe that the outcomes and operating time is less, that has been recently published by the ROLAR trial [11]. Similarly; to achieve good clinical and oncological outcomes with TaTME, surgeons are required to have performed at least 60 cases. Hence we decided to choose 60 procedures as an arbitrary number to select our surgeons experience involved in this trial.

### Potential benefits of TaTME rectal resections

TaTME offers better access to the lower rectum in a difficult pelvis and also facilitate a clear distal margin by insertion of a distal to the tumour purse string under direct vision. This enables an end-to-end anastomosis without the need of multiple stapler firings. This approach also allows two-team synergy with an abdominal and perineal surgeon operating simultaneously.

The technique however still requires significant surgical skills and the ability to operate in a confined space.

The objective of this study is to compare TaTME and RLAR in expert hands. Outcome measures are mainly focused on differences in oncological long-term effects, see ***Table 1*** for details.

**Table 1 T1:** Trial specific primary and secondary outcome measures.

OBJECTIVES	OUTCOME MEASURES	TIME POINT(S) OF EVALUATION OF THIS OUTCOME MEASURE (IF APPLICABLE)

**Primary Objective** 3 year disease free survival after RLAR and TaTME	3 year disease free survival	6 monthly post op for the first 2 years and 12-monthly follow-up for next 3 years

**Secondary/exploratory Objectives** Surgical morbidity/mortality up to 90 days		90 days

Pathological quality assessment	Pathological assessment of mesorectum: Distal resected margin ≥1 cm Lymph node yield Mesorectal plane of surgery R0 resection (all margins clear)	

Assessment of intraoperative adverse events	To report “near misses” and associated impact upon clinical outcomes	

Overall survival at 3 years		

Health economics assessments	Healthcare resource utilization (costs) including hospital length of stay, ICU hours, and productivity losses collected through a Labour Force survey). Return to work/activity will also be included	

Evaluation of the operative length of time	Total OR utilisation time and operative time skin to skin, minutes	

Recruitment per month per centre for the RLAR and TaTME arms	Patients dropout rate during follow-up will also be monitored	

## Methods/design

### Design

This is an observational prospective, multicentre trial. Patients will be assigned either RLAR or TaTME depends on the chosen centres. The centres do either TaTME or RLAR for rectal cancer management according to their training and experience. The study will include 330 patients from a number of international sites. This study has no impact on staging investigations, timing of surgery or any other aspect of the patients’ pre, peri or post-operative care. All decisions remain with the local clinician multi-disciplinary team including when to discharge from hospital. However, the biostatisticians performing the analysis will be blinded to the intervention. For study flow see ***Figure 1***.

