### The Number of Participants

The primary study end point, DFS is defined as the time following successful surgery to the first date of local, regional/distant relapse or death due to colorectal cancer (patients with secondary malignancy will be censored). Overall survival is defined as the time following successful surgery to death.

In the TaTME, it is assumed that the DFS is 92% and in the RLAR arm 95% at 3 years. A non-inferiority margin of 90% is selected. Based on this estimation, sample size calculation has been done with a one-sided level of significance of 20% and a power of 80%. A total number of 330 patients is needed, 165 patients in the RLAR arm and 165 patients in the TaTME are required with a 10% loss to follow-up assumed.

DFS will be analysed on an intent-to-treat (per protocol) basis using a log-rank test after propensity matching analysis has been conducted; a secondary analysis of DFS will also performed be using a Cox proportional hazards regression model with the unmatched cohort (without adjustment of baseline characteristics, i.e. propensity score match) that allowed for the effect of treatment and include lists of covariate with a statistical interaction of alpha level of 20%.

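### Technique is fixed by centre, but the log-rank test and the 330 treat patients as independent, so with any positive between-centre correlation the standard error is too small and the 80% power too high

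*Protocol article*

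**What the plan says.** The Design section of the protocol article describes an observational, prospective, multicentre study without randomisation. Technique follows the centre: "Patients will be assigned either RLAR or TaTME depends on the chosen centres". On what each site offers, the section adds: "The centres do either TaTME or RLAR for rectal cancer management according to their training and experience". The number of centres is left open: "The study will include 330 patients from a number of international sites". The same section leaves staging, timing of surgery and all other care to the local team.

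The section on the number of participants gives the planning inputs. On the expected rates it says: "In the TaTME, it is assumed that the DFS is 92% and in the RLAR arm 95% at 3 years". The margin follows, without a scale: "A non-inferiority margin of 90% is selected". On error and power it says "sample size calculation has been done with a one-sided level of significance of 20% and a power of 80" per cent. The result is stated as "A total number of 330 patients is needed, 165 patients in the RLAR arm and 165 patients in the TaTME" group, with 10% loss to follow-up as the only inflation named. The primary analysis of DFS is made "using a log-rank test after propensity matching analysis has been conducted". A secondary Cox model uses the unmatched cohort with covariates that are not listed. Nothing in the article mentions clustering by centre or surgeon, a design effect or an ICC.

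**The concern.** When each centre contributes one technique only, no within-centre comparison of the two techniques exists. The contrast between arms is a contrast between two sets of centres, and any centre-to-centre variation in DFS becomes part of it. An ordinary log-rank test takes its variance from patients as if they were independent, and so leaves that component out.

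Matching on patient variables does not restore independence, because every matched pair spans two centres. It can balance what is recorded per patient, including treatment received. It cannot remove unmeasured centre differences such as pathology or surveillance practice.

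The article itself gives grounds to expect variation between centres. The sites are international and local care is left unchanged. The Discussion reports an unexpectedly high local recurrence after TaTME in one national experience despite trained surgeons, with the reason unclear. The Conclusions intend treatment recommendations from this comparison. With a one-sided level already at 20%, a difference that belongs to a few centres could be credited to a technique.

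**Working it through.** **1. The plan's own figure.** The 330 cannot be reproduced from the stated inputs once the 10% loss is applied. All readings below use one-sided 20% and 80% power, with totals divided by 0.9.

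| Reading | Total with loss |
|---|---|
| Superiority, 92% v 95% (382 per arm) | 764 / 0.9 = 849 |
| 10-point margin, TaTME tested against RLAR | 158 |
| 10-point margin, RLAR tested against TaTME | 47 |
| 90% as a DFS floor, RLAR tested against TaTME (2 points) | 307 |
| 90% as a DFS floor, TaTME tested against RLAR (5 points) | 1907 |

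Two further readings come near 330 only if the loss is left out: 336 with the floor expressed as a hazard-ratio margin, and 334 with equal 92% rates and a 5-point margin. This is a separate fault. The steps below take the stated 80% power and 20% level at face value for independent patients, so that they show the effect of clustering alone.

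**2. Inputs.**
- Evaluable patients: 330 × 0.9 = 297 (from the article).
- z = 0.8416, the normal quantile for both the 20% level and 80% power. The standardised effect implied by the stated design is 2 × 0.8416 = 1.683.
- Number of centres k and ICC: assumptions, as the article gives neither.

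**3. Formulas.**
- Patients per centre: m = 297 / k, taken as equal.
- Design effect: DE = 1 + (m − 1) × ICC. The true standard error is √DE times the one the ordinary test uses.
- True one-sided error of the ordinary test: 1 − Φ(0.8416 / √DE).
- Power of a test that really holds 20%: Φ(1.683 / √DE − 0.8416).

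**4. Results.** For k = 10, m = 29.7. With ICC 0.01, DE = 1 + 28.7 × 0.01 = 1.287 and √DE = 1.134. The error is 1 − Φ(0.742) = 22.9% and the power is Φ(1.484 − 0.842) = Φ(0.642) = 74.0%.

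| Centres | ICC | DE | True one-sided error | Power at a true 20% level |
|---|---|---|---|---|
| 10 | 0.01 | 1.29 | 23% | 74% |
| 10 | 0.02 | 1.57 | 25% | 69% |
| 10 | 0.05 | 2.44 | 30% (29.5%) | 59% |
| 30 | 0.005 | 1.04 | 21% (20.5%) | 79% |
| 6 | 0.05 | 3.43 | 32% (32.5%) | 53% |

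The error column describes the ordinary log-rank test as planned. The power column describes a test corrected to a true 20%. If the ordinary test is kept, its power is Φ(0.8416 / √DE): 77%, 75% and 71% for the three 10-centre rows. That is also below 80%, and it comes with the inflated error. The power column uses normal quantiles; a t reference with few centres lowers it a little further.

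**5. What these ICCs mean.** At the average planned DFS of (92 + 95) / 2 = 93.5%, the between-centre SD is √(ICC × 0.935 × 0.065). ICC 0.01 gives 2.5 percentage points and ICC 0.05 gives 5.5. The planned difference between arms is 3 points.

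**6. Expected events.** 148.5 × 0.08 + 148.5 × 0.05 = 19.3, or about two per centre with 10 centres.

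**The case against.** The strongest objection is to size. Neither the number of centres nor the ICC is in the article, and the plausible range runs from about 1 power point lost to more than 25. An ICC of 0.05 means a between-centre SD of 5.5 points, nearly twice the assumed technique difference, among surgeons selected for at least 60 procedures. That is hard to believe as a central case. The baseline of 80% is itself unsupported, since 330 does not reproduce. Matching will also discard patients and change the cluster sizes, which the calculation ignores. All of this stands, and it limits the figures to illustration.

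A second objection is that a condensed article may leave the centre adjustment to a fuller plan. That is fair for the unnamed Cox covariates. It does not cover the primary test and the sample-size inputs, which the article states and which are at patient level. Nor would the usual devices help: stratifying by centre, or fixed centre effects, are aliased with technique.

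Third, a reader might infer that matching can do nothing about differences in neoadjuvant policy. The article does not support that. Neoadjuvant treatment received is a patient-level variable, the propensity covariates are not listed, and it can be balanced where the arms overlap.

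**Conclusion.** The point holds in direction for any positive between-centre correlation. As written, the primary test gives intervals that are too narrow, exceeds its one-sided 20% level, and has less power than stated.

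The size is not established. On the assumption of 10 equal centres and an ICC of 0.01 to 0.05, the true error is 23% to 30% and the power 74% to 59%, taking 80% as correct before clustering. With many small centres and a low ICC the loss is about 1 point; with 6 centres and an ICC of 0.05 power is 53%.

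Two stronger readings should be resisted. A reader might infer that clustering alone reduces the study to a particular low power; without the number of centres and an ICC, no single figure is supported. A reader might also infer that a corrected variance makes the comparison one of techniques. It corrects the error bars only, and the confounding of technique with centre remains.

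**What to change.** - Compute the primary DFS contrast with a cluster-robust or centre-jackknife variance, with centre as the cluster, and refer it to a t distribution on centres minus 2 degrees of freedom. Masked centre codes keep the statisticians blinded.
- State the number of centres and an assumed ICC, and restate the power at 330 with the resulting design effect. The 330 needs a reproducible derivation first.
- Do not stratify by centre or fit fixed centre effects, which are aliased with technique. With about 19 expected events, a shared frailty or several centre-level covariates should be at most a sensitivity analysis.
- State in the conclusions that technique and centre effects cannot be fully separated.

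The cost is wider intervals and a less favourable stated power. The analysis needs only each patient's centre, and Table 1 already plans to report recruitment by centre.

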**Figure 1 F1:**
[figure not shown]
ROTA Study flow.

### Study population

Participants with rectal cancer who are scheduled for initial treatment by TME by the MDT. The inclusion and exclusion criteria are shown in ***Table 2***.

**Table 2 T2:** Trial specific inclusion and exclusion criteria.

INCLUSION CRITERIA	EXCLUSION CRITERIA

Participant is willing and able to give informed consent for participation in the trial.	Female participant who is pregnant, lactating or planning pregnancy during the course of the trial.

Male or Female, aged 18 years or older.	Participant with life expectancy of less than 6 months.

TME surgery for rectal cancer after MDT discussion.	Any other significant disease or disorder which, in the opinion of the Investigator, may either put the participants at risk because of participation in the trial, or may influence the result of the trial, or the participant’s ability to participate in the trial.

Participant has no contra-indication to pelvic radiotherapy at the time of enrolment.	Participants who have participated in another research trial involving an investigational product in the past 12 weeks.

In the Investigator’s opinion, is able and willing to comply with all trial requirements.	

Tumour distance from anal verge – 12 cm or less	

Willing to allow his or her General Practitioner and consultant, if appropriate, to be notified of participation in the trial.	

### The Number of Participants

The primary study end point, DFS is defined as the time following successful surgery to the first date of local, regional/distant relapse or death due to colorectal cancer (patients with secondary malignancy will be censored). Overall survival is defined as the time following successful surgery to death.

In the TaTME, it is assumed that the DFS is 92% and in the RLAR arm 95% at 3 years. A non-inferiority margin of 90% is selected. Based on this estimation, sample size calculation has been done with a one-sided level of significance of 20% and a power of 80%. A total number of 330 patients is needed, 165 patients in the RLAR arm and 165 patients in the TaTME are required with a 10% loss to follow-up assumed.

DFS will be analysed on an intent-to-treat (per protocol) basis using a log-rank test after propensity matching analysis has been conducted; a secondary analysis of DFS will also performed be using a Cox proportional hazards regression model with the unmatched cohort (without adjustment of baseline characteristics, i.e. propensity score match) that allowed for the effect of treatment and include lists of covariate with a statistical interaction of alpha level of 20%.

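### DFS and OS are timed from successful surgery, an undefined post-operative result, so patients whose operation was not successful have no start time

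*Protocol article*

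**What the plan says.** All references are to the protocol article.

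- **The Number of Participants, primary endpoint:** "DFS is defined as the time following successful surgery to the first date of local, regional/distant relapse", or death due to colorectal cancer.
- **Same section, overall survival:** "Overall survival is defined as the time following successful surgery to death".
- **Abstract, Method:** the only place where success is defined. "Successful oncological and clinical outcomes are defined as circumferential resection margin (CRM) ≥1 mm with limited postoperative morbidity", the latter meaning "absence of Clavien-Dindo grade III–IV complications within 30 days after surgery".
- **Study population:** "Participants with rectal cancer who are scheduled for initial treatment by TME by the MDT". Patients therefore enter before the result of surgery is known.
- **The Number of Participants, analysis:** "DFS will be analysed on an intent-to-treat (per protocol) basis using a log-rank test after propensity matching analysis has been conducted".
- **Same section, planning values:** "it is assumed that the DFS is 92% and in the RLAR arm 95% at 3 years" for TaTME and RLAR respectively. "A non-inferiority margin of 90% is selected". The sample size is 165 per arm, 330 in total, at one-sided 20% and 80% power, with 10% loss to follow-up.

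No section gives a DFS or OS start time for a patient whose surgery was not successful.

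**The concern.** A time-to-event endpoint needs an origin that every patient in the comparison has. Here the origin exists only for patients whose operation turned out in a certain way. Margin status, completion of the resection and early complications are all effects of the operation, and the operation is what is being compared. If success depends on any of them, and their rates differ between TaTME and RLAR, the two groups with a defined DFS time are no longer comparable, however well they were matched at baseline.

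The article itself treats resection quality as a possible point of difference. The Background stresses the risk of an involved circumferential margin in low rectal surgery. The Discussion reports more distal margin involvement with TaTME in one comparison, and an unexpected local recurrence rate after TaTME in another report. Distal and circumferential margins are different measures, so this does not establish a difference in the success criterion. It does show that the authors consider a difference in resection quality plausible.

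**Working it through.** **1. Who has a start time under each reading**

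| Reading of successful surgery | Patients with no DFS or OS time |
|---|---|
| Abstract definition (circumferential margin ≥1 mm and no grade III–IV complication within 30 days) | Involved margin; major complication within 30 days |
| Operation completed | Abandoned operations; arguably incomplete resections |
| Date of operation, whatever the result | None among those operated on |

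Only the third reading gives every operated patient a time, and it is not what the text says. Under the first, success is not known until day 30, so it is also unclear whether the clock starts on the day of surgery or at day 30. Whether a patient who dies from the operation has an OS time is unclear under either of the first two.

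**2. Why the rest of the analysis does not repair it**

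Propensity matching balances characteristics measured before surgery. It cannot balance a selection that surgery itself produces. The analysis label names intention-to-treat and per-protocol together, which are different sets, and neither word supplies a missing time origin.

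**3. Possible distortion of the DFS difference (all rates assumed)**

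Let *p* be the share of unsuccessful operations in an arm, *r* the 3-year event risk after success (taken as equal in both arms), and *e* the excess risk after an unsuccessful operation. Event risk among all operated patients is *r + p·e*, so the between-arm difference that a success-only analysis hides is

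hidden difference = (*p*₂ − *p*₁) × *e*.

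- Involved margins differ by 2 points, excess relapse 25 points: 0.02 × 0.25 = 0.5 points.
- Involved margins differ by 5 points, excess relapse 40 points: 0.05 × 0.40 = 2.0 points.
- A second set of assumptions, 10% v 20% unsuccessful and *r* = 6%: with risk doubled, 0.10 × 0.06 = 0.6 points; with risk tripled, 0.10 × 0.12 = 1.2 points.

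The planned difference is 95 − 92 = 3 points. The first two lines cover margin failures only; no bias is estimated for complications.

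**4. Possible loss of numbers (share assumed)**

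After the stated 10% loss, 165 × 0.90 = 148.5 per arm, or 297 in total. The stated 330 does not reproduce from the stated inputs. Of the readings tried that use only those inputs, the closest takes the 90% as a margin of 2 points (92 − 90) with true DFS of 95% v 92%. It needs 138 per arm, or 154 with dropout, 308 in total. That is a separate matter and this point does not rest on it.

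On that reading the distance is 3 + 2 = 5 points and the variance sum is 0.95 × 0.05 + 0.92 × 0.08 = 0.1211. Power = Φ(0.05 / √(0.1211/n) − 0.8416):

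- n = 148.5: Φ(0.91) = 82%.
- 20% removed, n = 118.8: Φ(0.72) = 77%.
- 25% removed, n = 111.4: Φ(0.67) = 75%.

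If the comparison is instead a plain test of 95% v 92% at one-sided 20%, power is 58.2% with 297 patients. Removing 5% to 30% leaves about 282 to 208 patients and power of 57.2% to 51.4%. Both calculations hold 95% and 92% fixed after high-risk patients are removed, so they show only the effect of smaller numbers.

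**5. Direction**

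In the 82% model the arm tested for non-inferiority is assumed 3 points better. If removing failures shrinks that advantage, non-inferiority becomes harder to show. If the tested arm is truly worse and has more failures, removing them makes non-inferiority easier to show. The article does not say which arm is tested.

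**The case against.** The strongest reply is that *successful* was meant loosely. The Abstract defines successful oncological and clinical outcomes, not successful surgery, and neither place refers to the other. A criterion with a 30-day window fits poorly with a clock that starts at surgery. The Abstract's Discussion, Table 1 and the main Discussion all describe DFS after the two procedures without any success condition, and the analysis is labelled, in part, intention-to-treat.

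Much of this stands. A reader might infer that the plan excludes every patient with an involved margin or a major complication. The article does not state that exclusion, and the link to the Abstract is an inference. A reader might also infer that converted operations drop out under the looser reading; a converted operation can still be completed, and nothing in the article removes it. Nor does the article support a claim that the wording necessarily favours non-inferiority. Every failure rate and excess risk used above is an assumption.

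What does not stand is that the point is harmless or merely detail left for the analysis plan. The article defines the primary endpoint, and does so with a condition on the surgical result. The available readings give different analysis sets, and under neither the strict nor the loose one does every operated patient have a start time.

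**Conclusion.** The concern holds as a defect in the definition of the primary endpoint and of OS. Both are timed from an undefined post-operative result, with no origin for patients who do not meet it. Followed as written, this selects the comparison on a consequence of the technique and conflicts with the intention-to-treat part of a label that already contradicts itself.

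Confidence is high that the wording needs to change, and only moderate as to which reading was intended. The size cannot be computed from the article: 0.5 to 2.0 points of hidden DFS difference is an illustration that rests on a 2 to 5 point gap in involved margins, a 25 to 40 point excess in relapse, and equal risk after success in both arms. If failures were equally common and equally harmful in both arms, the hidden difference would be zero and only patient numbers would be lost. The effect on a non-inferiority conclusion depends on which arm is tested and which is truly worse.

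**What to change.** 1. Define DFS and OS from the date of the index operation for every enrolled patient whose operation was begun, regardless of margin status, complications or conversion.
2. State one rule for patients never rendered disease-free. Counting them as DFS events at day 1, with a sensitivity analysis under another convention, is one explicit option among several.
3. Keep margin status and complications as outcomes only. Table 1 already lists R0 resection and 90-day morbidity and mortality; if the composite success criterion in the Abstract is retained, report it separately as well.
4. Replace the combined intention-to-treat and per-protocol label with a single named primary analysis set.

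The cost is a few sentences in the protocol and analysis plan. The sample size and patient care do not change. The article does not list the contents of the case report forms, but 30-day and 90-day outcomes cannot be assessed without the operation date, so no new data item should be needed. The change should be made before any outcome data are compared by arm.

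### The primary endpoint, called disease-free survival, counts only colorectal-cancer deaths and censors at second malignancy, so fatal complications and other deaths are not failures when the two operations are compared

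*Protocol article*

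**What the plan says.** The section The Number of Participants ends DFS at the first relapse, whether local, regional or distant, or at "death due to colorectal cancer (patients with secondary malignancy will be censored"). The clock starts under a condition: "DFS is defined as the time following successful surgery". The next sentence gives overall survival the same start but no limit on cause: "Overall survival is defined as the time following successful surgery to death". The limit on DFS deaths is therefore part of the definition and not loose shorthand.

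For planning, "it is assumed that the DFS is 92% and in the RLAR arm 95% at 3 years". The primary analysis is a log-rank test after propensity matching, with a Cox model on the unmatched cohort as a secondary analysis. No competing-risk method is named.

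Table 1 places 3-year overall survival and "Surgical morbidity/mortality up to 90 days" among the secondary or exploratory objectives.

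The abstract's Method paragraph describes a successful outcome as a circumferential resection margin of at least 1 mm with limited morbidity, meaning "absence of Clavien-Dindo grade III–IV complications within 30 days after surgery".

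**The concern.** Readers take a 3-year DFS figure as the proportion alive and free of disease. Under this definition it is not. A patient who dies of an anastomotic leak or sepsis contributes to the log-rank test in the same way as one who left follow-up free of disease.

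This matters because two operations are being compared, and fatal complications are one way in which operations can differ. Technique is set by centre without randomisation, so censoring by such deaths may also be informative. Censoring at a second malignancy discards any later relapse or cancer death in those patients.

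The start of the clock adds to the problem. If the abstract's description of success governs DFS, a patient with a severe early complication or an involved margin has no start time. An early death after such a complication would then be lost whatever the event definition says.

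**Working it through.** **What follows from the text.** A death outside the definition is not an event, and in a log-rank or Cox analysis a non-event is censored. The article states censoring outright only for second malignancy; for non-cancer deaths it is a consequence of the definition and the named methods.

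**Inputs from the article.** 165 patients per arm (2 × 165 = 330), 10% loss to follow-up, and 3-year DFS of 92% (TaTME) and 95% (RLAR). The stated inputs do not lead to 330 under the readings tried, but that is a separate matter; only the stated arm size is used here.

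**Events as defined.** Evaluable per arm: 165 × 0.90 = 148.5.
- TaTME: 148.5 × 0.08 = 11.9
- RLAR: 148.5 × 0.05 = 7.4
- Total: 19.3

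**Counting all deaths.** Let q be the 3-year probability of non-cancer death. The article does not give it, so q is an assumption. If it is independent of relapse and cancer death, all-death DFS = stated DFS × (1 − q). With q equal in both arms:

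| q | TaTME | RLAR | Events, all deaths | Share left out by the written definition |
|---|---|---|---|---|
| 1% | 91.08% | 94.05% | 148.5 × (0.0892 + 0.0595) = 22.1 | (22.1 − 19.3)/22.1 = 13% |
| 2% | 90.16% | 93.10% | 148.5 × (0.0984 + 0.0690) = 24.9 | 22% |
| 3% | 89.24% | 92.15% | 148.5 × (0.1076 + 0.0785) = 27.6 | 30% |
| 5% | 87.40% | 90.25% | 148.5 × (0.1260 + 0.0975) = 33.2 | 42% |

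The 19.3 is held fixed. Deaths that come before a relapse would lower it by at most 19.3 × 0.05 = 1.0 event at q = 5%, so the shares shown are slightly low.

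**Effect on the contrast.** The stated gap is 95 − 92 = 3 points.
- Equal q: the gap is 3 × (1 − q), that is 2.97 points at 1% and 2.85 at 5%. It hardly changes.
- q = 3% TaTME, 1% RLAR: 0.95 × 0.99 − 0.92 × 0.97 = 0.9405 − 0.8924 = 4.8 points.
- q = 1% TaTME, 3% RLAR: 0.95 × 0.97 − 0.92 × 0.99 = 0.9215 − 0.9108 = 1.1 points.

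No rate of second malignancy is given, so the loss from that censoring is not quantified.

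**The case against.** The best defence is that this is a choice of estimand. The article says its outcomes centre on long-term oncological effects, and its Discussion is motivated by reports of local recurrence after TaTME. A cancer-specific endpoint suits that aim, and a log-rank test with other deaths censored is a recognised comparison of cause-specific hazards. That much stands: a renamed endpoint with other deaths handled as competing events would be coherent. As written, though, the endpoint carries a name that promises survival, and no competing-risk handling is given.

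Several stronger readings are tempting but unsupported:
- **That a mortality difference would be hidden altogether.** Overall survival and 90-day mortality are listed outcomes; the deaths leave the primary endpoint, not the trial.
- **That the definition pulls the arms together.** With equal rates the gap is almost unchanged, and with unequal rates it can move either way.
- **That sites aware of the technique decide the cause of death.** The article does not say who attributes cause. It mentions blinding only for the biostatisticians, and adjudication is a detail that the full protocol may hold.
- **That a 2-point mortality difference uses up the distance from 92% to 90%.** The 90% margin has no stated scale, so it cannot be read as a DFS floor.

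It is also fair to say that the article does not state that the abstract's success criteria govern the start of DFS; that link is possible, not established.

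**Conclusion.** The concern holds. Under the definition and the named analyses, postoperative and other non-cancer deaths are not failures in the primary comparison, and follow-up for relapse stops at a second malignancy. Both follow from the article's wording and depend on no assumed rate.

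The size does depend on one. At an assumed 1% to 5% non-cancer mortality by 3 years, equal in both arms and independent of relapse, about 13% to 42% of all-death DFS events are left out. With so few counted events, a 2-point difference in such mortality between arms would move the 3-point contrast by almost 2 points in either direction. The direction cannot be predicted from the documents.

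**What to change.** 1. Define the DFS event as first local, regional or distant recurrence or death from any cause. Do not censor at second malignancy; continue to record relapse and death.
2. Start the clock at the date of surgery for every operated patient, so that early deaths and complicated cases have a start time. Apply the same origin to overall survival.
3. Keep the present definition as a cancer-specific sensitivity analysis, with other deaths as competing events.
4. Restate the 92% and 95% assumptions, and the margin with its scale, for the all-death endpoint.
5. As a minor separate correction, let the abstract's success definition read grade III–V, so that a 30-day death cannot count as limited morbidity. Do not use that definition to decide who enters the DFS analysis.

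Deaths are already needed for overall survival, so little new data collection is involved. The cost is more than wording: the assumed rates fall (to 90.2% and 93.1% at an assumed q of 2%, for example), and the sample-size text has to be restated.
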